## 5. Statistical Analysis

To ensure the integrity and accuracy of data, two statisticians will independently perform statistical analyses using Statistics 26.0 (IBM SPSS Statistics Inc., Chicago, USA), establish the database, and provide proofreading for logic. Enumeration data will be expressed as percentages, whereas measurement data will be expressed as mean ± standard deviation. A normality test will be performed for the measurement data. For variables that are determined to be regularly distributed, a *t*-test will be employed, and for those that are not, a rank-sum test will be utilized. The rank-sum test and nonparametric test will be employed for graded data, and the chi-square test will be applied to counted data. Repeated-measures analysis of covariance (ANCOVA) will be used for the UPDRS, Hoehn–Yahr, HAMA, and SF-36 scales. The rank-sum test will be applied to compare efficacy. Serological index values will be analyzed using covariance. Two-sided tests will be used for all hypothesis testing, with *P* < 0.05 as the standard of statistical significance.

Stage Two: if the efficacy of acupuncture with anti-Parkinson drugs for PDA is found to be better than that of the sham acupuncture, excluding the possible placebo effect of acupuncture, stage 2 will be conducted to assess the compliance, viability, universality, and cost effectiveness of acupuncture for PDA.  Figure 6 depicts a flowchart of the second step.Diagnostic criteria:  The diagnostic criteria for stage 2 are the same as those for stage 1Participant inclusion criteria:  The inclusion criteria for stage 2 are the same as those for stage 1Participant exclusion criteria:  The exclusion criteria for stage 2 are the same as those for stage 1

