## Abstract

Parkinson's disease anxiety (PDA) is a nonmotor symptom of Parkinson's disease (PD) that is often neglected. PDA poses a far-reaching challenge to the treatment of PD. Acupuncture could be successful in the treatment of PDA. However, the evidence for this is still limited. We propose a two-stage clinical trial. In stage 1, a total of 70 volunteers with PDA will be randomly assigned to either acupuncture (manual acupuncture) or control group (sham acupuncture) in a 1 : 1 ratio. Treatments will be performed for four weeks. The change in the Hamilton Rating Scale for Anxiety (HAMA) score from baseline to week 4 and week 12 will be the primary outcome. The levels of adrenocorticotropic hormone (ACTH), cortisol (CORT), serotonin (5-HT), and corticotropin-releasing factor (CRH) in the patients' serum and the scores on the Hoehn–Yahr Rating Scale and the Unified Parkinson's Disease Rating Scale (UPDRS) will all be considered among the secondary outcomes. Participants will be followed up until week 12. In stage 2, a total of 82 volunteers with PDA will be randomly assigned to either an acupuncture (manual acupuncture) or a control group (anti-Parkinson drugs only) in a 1 : 1 ratio. HAMA score will be the primary outcome. Universality, feasibility and cost effectiveness, Hoehn–Yahr Rating Scale, UPDRS, and serological indicators will be secondary outcomes. Participants will be followed up until week 4. The statistical analysis will include all the allocated individuals. The First Affiliated Hospital of Guangzhou University of Traditional Chinese Medicine's Research Ethical Committee authorized this procedure, and the trial is registered with ChiCTR2100047253.

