### 3.4. Primary Outcome

The change in the HAMA score from baseline will be the primary outcome, measured at baseline and week 4. We will also use this scale during the follow-up period at week 12 to assess the anxiety status of the patients after they leave the group. HAMA is one of the first rating scales used to measure the severity of perceived anxiety symptoms and is often used in clinical trials. It consists of 14 symptomatic definition elements that reflect psychological and physical symptoms. Each item is rated on a scale of 0 to 4, for a total possible score of 56. Mild anxiety is indicated by a score of 17–24, whereas severe anxiety is indicated by a score of 25–30.

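### Stage 1 states several tests that can apply to the primary HAMA change and never says which is confirmatory; with free choice among them the type I error is about 8% to 9%, not 5%

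*Protocol article*

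**What the plan says.** Section 3.4 of the protocol article defines the primary outcome: "The change in the HAMA score from baseline will be the primary outcome, measured at baseline and week 4". Week 12 is described there as follow-up. The abstract differs and makes the change in HAMA "score from baseline to week 4 and week 12 will be the primary outcome".

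Section 5 (stage 1) then gives three rules in one paragraph:

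- **Measurement data in general.** "A normality test will be performed for the measurement data". Normal variables go to a t-test; "for those that are not, a rank-sum test will be utilized". HAMA is not excepted.
- **HAMA by name.** "Repeated-measures analysis of covariance (ANCOVA) will be used for the UPDRS, Hoehn–Yahr, HAMA, and SF-36 scales". The covariate, the visits in the model and the tested term (group, or group by time) are not stated.
- **Efficacy.** "The rank-sum test will be applied to compare efficacy". The variable meant by efficacy is not defined.

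The same section makes stage 2 conditional on acupuncture's efficacy, which must be shown in that it "is found to be better than that of the sham acupuncture". It does not say which test decides. Section 6.1 repeats the three rules for stage 2, with repeated-measures ANOVA in place of ANCOVA. On the analysis population, the abstract says: "The statistical analysis will include all the allocated individuals".

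**The concern.** The rules answer different questions. A t-test on change compares mean change at week 4. A rank-sum test compares distributions. A repeated-measures ANCOVA over weeks 4 and 12 gives either an average group difference across visits or a test of whether that difference varies with time, depending on the term that is read. With no order among them, the primary P value can be chosen after the results are seen.

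Two decisions rest on that P value: the stage 1 conclusion, and whether to start stage 2, which is planned to randomise 82 more patients. A later statistical analysis plan could not simply fill in a detail here. It would have to choose between sentences already published.

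**Working it through.** **1. The plan's own figure.** Section 2.5 gives means of 15.3 and 13.2, a two-sided 5% level, 80% power and 31 per group. The difference is 15.3 − 13.2 = 2.1. No SD is stated, so 31 cannot be confirmed, only inverted. From n = 2σ²(1.960 + 0.842)²/δ², σ = 2.1 / (√(2/31) × 2.802) = 2.1 / 0.712 ≈ 2.95. The dropout step reproduces: 31/0.9 = 34.4, so 35 per group and 70 in total. The section names software but no test, so it does not show which analysis the trial was sized for.

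**2. Which rules can reach HAMA change.**

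| Rule in section 5 | How it reaches HAMA | What it tests |
|---|---|---|
| Normality test, then t or rank-sum | HAMA change is measurement data | Week-4 change, by mean or by rank |
| Repeated-measures ANCOVA | Named | Not stated: group or group by time |
| Rank-sum for efficacy | Only if efficacy means HAMA change | Ranks |

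Stage 2 has HAMA at baseline and week 4 only. With two visits and complete data, the group-by-time test of a repeated-measures ANOVA equals the t-test on change, but the group main effect averages in the baseline. The unstated term therefore matters there too.

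**3. Size of the choice under no effect.** From the document: 31 per arm, two-sided 5%. Assumed: correlation 0.3, 0.5 or 0.7 between any two visits; normal or log-normal scores; complete data; the ANCOVA read as the group effect on the mean of weeks 4 and 12, adjusted for baseline; the pretest taken as Shapiro-Wilk in each arm. With 4,000 null trials per setting:

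| Reading | Type I error |
|---|---|
| Pretest, then t or rank-sum | 4.3% to 5.6% |
| Rank-sum on change | 4.2% to 5.3% |
| Repeated-measures ANCOVA | 4.5% to 5.2% |
| Any of the three | 8.3% to 9.2% |

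The simulation error near 8.5% is √(0.085 × 0.915/4000) ≈ 0.4 percentage points. A separate run under the same range of correlations gave 8.2% to 8.9% for any of the three. It gave 7.6% to 8.4% when only the pretest route and the ANCOVA are allowed. A repeat of that two-route case with 6,000 trials per setting, skewed scores included, gave 8.0% to 9.1%. Removing the efficacy rule therefore changes little.

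**4. How often the routes disagree.** The three routes split on significance in 6.7% to 7.9% of null trials. With normal scores and an effect set to give the t-test on change 80% power, assumed to persist in full to week 12, they split in about 20% to 24% of trials (3,000 per setting).

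**The case against.** Only the ANCOVA sentence names HAMA. The rule for measurement data is generic, and a specific rule may be taken to override it. The efficacy sentence does not mention HAMA; since the section also uses rank-sum tests for graded data, efficacy could be a graded response that the article does not describe. The 8% to 9% further assumes that any significant route would be reported. These points stand. A reader might infer that the plan literally assigns HAMA to three tests, and it does not. But the article never says that the specific rule overrides the generic one, nor what efficacy is, and the two-route result shows that the problem remains if efficacy means something else.

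Three stronger readings are not supported:

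- *The ANCOVA discards incomplete patients.* A classical repeated-measures procedure needs every visit, so it would leave out a patient with week-4 but no week-12 HAMA. The article gives neither the fitting method nor a missing-data rule, and both may sit elsewhere. This is a risk to reconcile with the abstract's inclusion of everyone allocated. The number affected is unknown. The planned 10% dropout is not that number, because patients lost before week 4 would be missing from a week-4 analysis as well. Nor is power the issue: 35 × 0.9 = 31.5 per arm, against the 31 required.
- *Averaging over weeks 4 and 12 contradicts analysing everyone allocated.* Averaging concerns what is estimated, not who is analysed, and the abstract itself lists both weeks as primary.
- *The normality pretest is harmful by itself.* Alone, it held 4.3% to 5.6%.

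**Conclusion.** The point holds as a conflict among stated rules. Section 5 contains at least two tests that can apply to the primary HAMA change, and a third if efficacy means HAMA change, with no confirmatory test named; section 6.1 does the same for stage 2. Free choice raises the stage 1 type I error from 5% to about 8% to 9%, or to roughly 8% to 9% at most if only the pretest route and the ANCOVA compete. These sizes rest on 31 per arm, assumed correlations of 0.3 to 0.7, complete data and the averaged group effect as the ANCOVA term. They exclude any further choice between weeks 4 and 12, which is a separate question. The loss of patients without week-12 data is conditional on a complete-profile fit and cannot be sized from the article. The point should be settled before the data are analysed, because both the stage 1 conclusion and the start of stage 2 depend on it.

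**What to change.** - Name one primary analysis for stage 1. Either use ANCOVA of week-4 HAMA on treatment group and baseline HAMA, or a likelihood-based mixed model of weeks 4 and 12 (group by visit, baseline by visit) with the week-4 contrast as primary. Report the adjusted mean difference and 95% CI by randomised group.
- Say how patients without a week-4 score, or with week 4 but not week 12, enter that analysis, so that it agrees with the abstract.
- Remove the normality pretest for HAMA and label the rank-sum test as a sensitivity analysis.
- Define efficacy as a variable or delete the sentence, and tie the condition for starting stage 2 to the named test.
- Make the abstract and section 3.4 agree on whether week 12 is primary.
- In section 6.1, name one baseline-adjusted primary test of week-4 HAMA in the same way.

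The cost is a few sentences of analysis wording. SPSS, already chosen, can fit either model. Data collection and sample size do not change.

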### 5.1. Sample Size

The sample size was calculated using the primary outcome, which is the shift in HAMA score from baseline. According to preliminary results, the mean HAMA score in patients who received acupuncture combined with anti-Parkinson drugs was 15.8, while it was 13.9 in patients who received anti-Parkinson drugs alone. According to PASS 15.0, a sample size comprising 74 patients (37 in each group) would have a power of 80% or more to identify a two-sided significance level of 5%. The overall sample size needed for the study is 82 (41 in each group), anticipating a 10% dropout rate. If a patient cannot adhere to a course of acupuncture, patient's condition suddenly worsens during the treatment process, and the treatment plan of anti-Parkinson drugs needs to be changed, the treatment will be stopped.

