### 2.5. Sample Size

The sample size was calculated using the primary outcome, which is a shift in the HAMA score from baseline. According to preliminary results, the mean HAMA score in patients who received acupuncture combined with anti-Parkinson drugs was 15.3, while it was 13.2 in patients who received the sham acupuncture with anti-Parkinson drugs alone. Using SPSS Statistics 26.0 (IBM SPSS Statistics Inc., Chicago, USA), we determined that a sample comprising 62 patients (31 in each group) would have a power of 80% or more to identify a two-sided significance level of 5%. The overall sample size needed for the study is 70 (35 in each group), anticipating a 10% dropout rate. If the patient cannot adhere to a course of acupuncture, patient's condition suddenly worsens during the treatment process, or the treatment plan of anti-Parkinson drugs needs to be changed, the acupuncture regimen will be stopped.

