## 3. Interventions

### 3.1. Acupuncture Group

Participants assigned to the acupuncture group will receive twelve 30 min sessions of acupuncture (once every other day, four times a week for four weeks) with clinical monitoring only (CMO) and maintain their original dosage of anti-Parkinson drugs. If the dosages need to be increased or decreased during the trial to relieve symptoms, the change will be recorded on the case report form. Patients in the intervention group will receive needling at traditional acupuncture points, including GV 24 (*shen ting*), GV 29 (*yin tang*), bilateral HT7 (*shen men*), bilateral SP 6 (*san yin jiao*), and *Si Shen Zhen* (four acupoints, consisting of GV 21, GV 19, and 1.5 cun next to GV 20 bilaterally, with the width of the patient's thumb joint being taken as one cun). The acupoints' positions are described by the National Standard of the People's Republic of China's (GB/T 12346–2006) standard for the name and location of the acupoints, which was established in 2006. Acupuncture will be performed with disposable, sanitized stainless steel needles (Tianxie, Suzhou Medical Appliance Factory, Suzhou, China; 0.25 × 25 mm, 0.25 × 40 mm). GV 24 (*shen ting*), GV 29 (*yin tang*), and *Si Shen Zhen* adopt 0.25 × 25 mm acupuncture needles with a 45-degree angle. Bilateral HT7 (*shen men*) and bilateral SP 6 (*san yin jiao*) will use 0.25 × 40 mm acupuncture needles with a 90-degree angle. The selection and location of the acupoints are shown in Figure 2. After routine disinfection, the acupuncturist inserts the needles into the corresponding acupoints and stimulates all the needles by lifting, twirling, and thrusting to obtain the *de qi* sensation (a combination of feelings, such as numbness, soreness, and heaviness).

CMO will involve providing patients with general educational leaflets on dealing with anxiety that were retrieved from web portals of the French and Netherlands psychiatric associations.

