### 3.2. Control Group

Participants assigned to the control group will receive twelve 30 min sessions of acupuncture with sham acupuncture needles (once every other day, four times a week for four weeks) with CMO and maintain the original dosage of their anti-Parkinson drugs. If dosages need to be increased or decreased during the trial to relieve symptoms, the change will be recorded on the case report form. For GV 24 (*shen ting*), GV 29 (*yin tang*), and *Si Shen Zhen*, 0.25 × 25 mm acupuncture needles with a 45-degree angle will be used. For Bilateral HT7 (*shen men*) and bilateral SP 6 (*san yin jiao*), 0.25 × 40 mm acupuncture needles with a 90-degree angle will be used. In this study, some acupoints need to be penetrated at an angle of 15°. This acupuncture tool consists of a base sticking to the skin and a sleeve. In particular, there are two types of bases in this acupuncture tool, one is hollow while the other is sealed by the adhesive layer. Specifically, we will paste this special acupuncture tool on the skin first. In the acupuncture group, we will put acupuncture needles through the cannula and pierce them into the skin through the perforated base to achieve the acupuncture effect. However, when used in the control group, a special placebo needle will be used to pass through the cannula and pressed against the adhesive layer and the skin, and a slight pressure will be applied to ensure a placebo effect similar to acupuncture. In this way, we hope to achieve a single-blind effect on the patients to verify the placebo effect in acupuncture. Figures 3–5 show the structure of the sham acupuncture needle.

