### 5.2. Interventions

#### 5.2.1. Acupuncture Group

Interventions for the acupuncture group in stage 2 will be the same as those in stage 1.

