#### 5.2.2. Control Group

Participants in the control group will be required to obtain CMO and maintain the original dosage of their anti-Parkinson drugs. If the dosages need to be increased or decreased during the trial to relieve symptoms, the change will be recorded in the case report form.

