To reduce bias, we will use a rigorous allocation method with blinded patients, evaluators, and statistical analysts. We will also use a new type of sham acupuncture tool to avoid the placebo effect. Therefore, this trial will potentially provide valid clinical evidence. However, this study has certain limitations. First, owing to the nature of acupuncture, the operator cannot be blinded in this study. However, we will ensure the blinding of the participants, evaluators, and statistical analysts. Second, although we strictly require no increase or decrease of the medication dosage of the participants during treatment, it is difficult to monitor the self-medication of patients. Third, although a strict sample size calculation was carried out for this study, the participants will be recruited from only one hospital, which may lead to a lack of representativeness of the data.

Whether a treatment measure is suitable for clinical application and promotion needs to be comprehensively considered from the aspects of clinical efficacy, cost and economic benefits, patient acceptance, and feasibility. Therefore, this study has two stages. Stage 1 of this study hypothesizes that patients with PDA receiving acupuncture will have a reduction in anxiety as a result of adjustments to the HPA on the basis of excluding the placebo effect. Stage 2 of this study hypothesizes that acupuncture to relieve PDA has the characteristics of high feasibility, fewer side effects, high patient compliance, and reasonable cost effectiveness. It will not add additional economic burden to patients and their families while providing a curative effect and improving the quality of life of patients. It is a treatment method with clinical promotion and application value. The second stage is a supplement to the first stage. We designed this two-stage trial to observe whether acupuncture has clinical application value in the treatment of PDA.

The findings of this study will help to validate the effects and mechanism of acupuncture as a complementary treatment method for PDA. The study has the potential to provide strong clinical evidence as well as new guidelines for the treatment of PDA.

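### The stage 2 stop rule in section 5.1 joins its three conditions with *and* and stops *the treatment*; section 2.5 joins the same three with *or* and stops *the acupuncture regimen*

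*Protocol article*

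**What the plan says.** Both stages name three conditions under which treatment is stopped: the patient cannot keep to the acupuncture course, the patient deteriorates suddenly, and the anti-Parkinson drug plan has to change. In both stages the rule stands at the end of the sample size section.

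- Stage 1, section 2.5, closes the list with: "or the treatment plan of anti-Parkinson drugs needs to be changed, the acupuncture regimen will be stopped".
- Stage 2, section 5.1, closes it with: "condition suddenly worsens during the treatment process, and the treatment plan of anti-Parkinson drugs needs to be changed, the treatment will be stopped".

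Section 5.2.1 then states: "Interventions for the acupuncture group in stage 2 will be the same as those in stage 1". Section 5 gives stage 2 the same inclusion and exclusion criteria as stage 1. Under section 5.2.2, stage 2 controls receive clinical monitoring (CMO) and their existing drugs, with no needling.

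On medication, Table 1 marks the medication status row at weeks 0 and 12, and Table 2 marks it at week 0 only. HAMA is marked at weeks 0, 4 and 12 in Table 1 and at weeks 0 and 4 in Table 2. Sections 3.4 and 5.2.3 measure the primary HAMA outcome at baseline and week 4. The Discussion concedes that "it is difficult to monitor the self-medication of patients".

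**The concern.** A stop rule is an instruction to the people who treat the patients. With *or*, any one condition ends needling. With *and*, taken at its word, all three must be present. A stage 2 patient who worsens abruptly but attends every session and needs no drug change would not meet the rule. Sudden worsening alone should be enough in both stages, because the needling and the eligibility criteria are the same.

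The object of the rule also changes. Stopping *the acupuncture regimen* is clear. Stopping *the treatment* is looser in a stage where one arm's treatment consists of anti-Parkinson drugs and CMO, and nobody can intend those drugs to be withdrawn.

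The secondary matter is the schedule. The visit at which the primary HAMA is taken has no planned check of current medication in either stage.

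**Working it through.** No figure in the plan depends on this point, so the check is a comparison of texts, a short piece of logic and a reading of the two tables.

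**1. The two rules side by side**

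| Element | Stage 1 (2.5) | Stage 2 (5.1) |
|---|---|---|
| A: cannot keep to acupuncture | listed | listed |
| B: sudden worsening | listed | listed |
| C: anti-Parkinson plan must change | listed | listed |
| Connector | *or* | *and* |
| What stops | the acupuncture regimen | the treatment |

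The conditions match one for one. Only the connector and the object differ.

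**2. What the connector does**

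Three yes/no conditions give 2 × 2 × 2 = 8 possible patient states.

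- A *or* B *or* C stops needling in every state except none present: 8 − 1 = 7 states.
- A *and* B *and* C stops needling only when all are present: 1 state.
- The rules therefore disagree in 7 − 1 = 6 of the 8 states, including B alone and C alone.

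This counts logical states, not patients. The documents give no rate for any of the conditions, so it cannot be turned into an expected number of stops.

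A softer parsing of 5.1 takes A by itself, or B together with C. Sudden worsening alone still does not stop needling under it. The wording has to change on either reading.

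**3. Could the design justify a different rule?**

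Section 5.2.1 makes the acupuncture the same and section 5 makes the eligibility the same. The two stages differ in the comparator, the blinding and the length of follow-up. None of these is a reason to keep needling a patient who has suddenly worsened.

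**4. Who is covered**

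The planned stage 2 acupuncture arm is 82 / 2 = 41 patients.

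**5. Medication status against HAMA visits**

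| | HAMA visits | Medication status | Coverage |
|---|---|---|---|
| Table 1 (stage 1) | weeks 0, 4, 12 | weeks 0, 12 | 2 of 3 |
| Table 2 (stage 2) | weeks 0, 4 | week 0 | 1 of 2 |

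The uncovered visit is week 4 in both stages. Sections 3.1, 3.2 and 5.2.2 provide a running record of dose changes, but it concerns anti-Parkinson drugs. The Discussion says that antianxiety and antidepressant drugs are what is mainly used for this anxiety, and the exclusion criteria in 2.4 do not explicitly bar them. The table row does not say which drugs it covers.

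**The case against.** **The literal reading is implausible.** An all-three rule would keep needling someone who cannot keep to acupuncture until two more events occurred, and section 5.2.1 points towards the stage 1 rule. This is a good argument that the authors meant *or*, and it is why the point is treated as a probable slip. It does not remove the error. Section 5.1 states its own rule for stage 2, and an investigator should not have to infer the intended one from another section.

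**Other safeguards exist.** Table 2 schedules adverse events and a safety assessment in each of weeks 1 to 4. That stands, and it lowers the practical risk. However, no other sentence in the article says when stage 2 needling is to stop.

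**The rule addresses needled patients only.** Its opening condition concerns acupuncture, so *the treatment* can fairly be read as the needling. This largely stands. The change of object is a clarification that accompanies the main correction.

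**A reader might also infer that the rules on anti-Parkinson dose changes contradict each other.** The Discussion says "we strictly require no increase or decrease of the medication dosage of the participants during treatment". Section 3.1 says "If the dosages need to be increased or decreased during the trial to relieve symptoms, the change will be recorded", section 3.2 says "If dosages need to be increased or decreased during the trial to relieve symptoms, the change will be recorded", and section 5.2.2 likewise says "the change will be recorded in the case report form". Section 2.5 makes a needed change of drug plan a reason to stop. The documents do not support a contradiction. Keeping the dose, recording a needed change, and stopping needling if the plan must change is a coherent sequence. Recording does not exclude stopping, a dosage need not be the same as a treatment plan, and the Discussion sentence describes a limitation. How such patients enter the per-protocol set is commonly left to the analysis plan.

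**The week-4 medication entry is a level of detail an article may omit.** In part this is fair. Baseline status plus the running record already covers reported anti-Parkinson changes. Nor would the entry reveal unreported self-medication, since nothing suggests it would rest on anything but the patient's account. It remains worth adding because the tables fix a schedule that leaves out the primary visit, and it is offered as an improvement only.

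**Conclusion.** The inconsistency between 5.1 and 2.5 is real and should be corrected before stage 2 opens. It is probably a drafting slip, but it stands in an operative rule that protects patients. Its reach is the needling of the 41 planned stage 2 acupuncture patients. The conclusion rests only on the two sentences and on the statement that the acupuncture is unchanged.

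A reader might go further and infer a threat to the sample size, because each arm has an allowance of only 4 patients for dropout (35 − 31 in stage 1, 41 − 37 in stage 2). The documents do not support this. It would require that a stop also ends HAMA collection, which the text does not say. The direction is also wrong, since the literal *and* produces fewer stops than *or*. No effect on the HAMA difference, power or dropout is claimed, and with no event rates given none can be calculated.

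The missing week-4 medication entry is a secondary point: a gap in scheduled assessment, with limited yield because it depends on patient report.

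**What to change.** 1. In section 5.1, change *and* to *or* before the third condition, and *the treatment* to *the acupuncture regimen*, so that the stage 2 rule matches section 2.5. The cost is two wording changes.
2. As a cheap improvement, mark medication status at week 4 in Tables 1 and 2 and state that it includes antianxiety and antidepressant drugs. The cost is one case report form entry at a visit that already takes place.

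Neither change alters the sample size, the outcomes or the analysis.
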